### 2.5. Variables

Demographic, clinical, analytical, microbiological, ultrasound, SWE, and SMI variables will be collected (Table 2).

### 2.6. Ethical Considerations and Data Collection

The study will be conducted in accordance with the ICH E11 Guideline and the Declaration of Helsinki (version Fortaleza, Brasil 2013). The study protocol has been approved by the Ethics Committee of Sant Joan de Déu Hospital. Patients will be enrolled by the study investigators after verifying that all inclusion criteria are met. The confidentiality of patient identities will be maintained throughout the study, and all data will be handled in compliance with Organic Law 3/2018 on the Protection of Personal Data. In accordance with this law, only data necessary to achieve the study’s objectives will be collected. Given that the study population will consist of critically ill paediatric patients, informed consent will be obtained from the legal representatives of these patients in all cases. Complete identifying information and written consent will be securely stored in the researcher’s files. A REDCAP database has been developed and securely hosted in a restricted-access cloud environment. This database includes automatic inconsistency detection filters to ensure data accuracy and provides full traceability of all recorded data. Access to the database will be limited to physicians and clinical researchers directly involved in the study, the Ethics Committee, and relevant health authorities, ensuring strict compliance with regulatory and ethical standards.

### 2.7. Statistical Analysis and Sample Size

To determine the normal reference values of elastance and microvascularization ratio in the healthy lung, measures of central tendency (mean and median) and dispersion (standard deviation, interquartile range) will be calculated for both elastance and microvascularization variables. The distribution of the variables will be assessed using the Shapiro–Wilk test to determine if the data follows a normal distribution. If the variables follow a normal distribution, the standard approach will be applied using the Faulkenberry-Weeks approach implemented in the tolerance R package. If the variables deviate from normality, non-parametric bootstrap methods will be used to estimate the tolerance intervals. Variability of the biomarkers across different patient subgroups (e.g., by sex or age) will be explored using analysis of variance (ANOVA), provided the assumptions of ANOVA are met. If assumptions are not met, permutation tests will be applied. A *p*-value of less than 0.05 will be considered statistically significant for all statistical tests. A sample of 60 subjects is considered sufficient to obtain 90% tolerance intervals at 95% confidence with a 5% error in tolerance and a 2.5% error in confidence [30].

Subsequently, to establish differences in the values of the imaging biomarkers among the different groups (BP, atelectasis, and normal baseline), analysis of variance (ANOVA) will be performed. In the event of finding significant differences, post-hoc analysis will be conducted using Tukey’s method. If the conditions for the applicability of ANOVA are not met, a permutation test will be applied. The sample size for the ANOVA test is calculated using the method proposed by Cohen. According to this method, the test effect size is the ratio of the sum of squares between groups to the total sum of squares. Cohen suggested a value of 0.25 as a medium effect size. The sample size is calculated using the pwr R package, which gives a sample size of 53 subjects per group required to detect a medium effect size with 80% power and three groups [31].

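### The precision stated for the 60-subject tolerance interval is not what 60 subjects give as worded; the two error figures appear mislabelled

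*Protocol article*

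**What the plan says.** The first outcome in section 2.2 of the protocol article is the set of normal biomarker values in healthy lung. Section 2.7 plans tolerance intervals for these values. If the data look normal, "the standard approach will be applied using the Faulkenberry-Weeks approach implemented in the tolerance R package". If they do not, "non-parametric bootstrap methods will be used to estimate the tolerance intervals".

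The sample size follows in one sentence. "A sample of 60 subjects is considered sufficient", it says, to "obtain 90% tolerance intervals at 95% confidence with a 5% error in tolerance and a 2.5% error in confidence", with a citation.

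The article defines neither error and does not say whether the interval is one- or two-sided. It gives no separate sample-size basis for the bootstrap branch.

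**The concern.** A tolerance interval has two basic settings: the content (here 90% of the population) and the confidence that this content is reached (here 95%). Many sample sizes meet both, because a small sample simply gives a wider interval. The Faulkenberry-Weeks criterion fixes n by adding a limit on excess width: the interval may cover a larger content P′ only with a small probability δ.

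The sentence has just used tolerance for the content and confidence for a probability. Its plain meaning is therefore a 5-point error in content (P′ = 0.90 + 0.05 = 0.95) and a 2.5% error in probability (δ = 0.025). That describes a tight interval, and 60 subjects looked too few for it.

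At stake is the precision claimed for the first listed outcome. A reader of the reference values would believe that the limits overshoot 95% coverage very rarely, when they may do so often.

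**Working it through.** **Inputs.** From section 2.7: n = 60, content P = 0.90, confidence 0.95, and the two error figures 5% and 2.5%. Assumed: a normal distribution; a two-sided interval (mean ± k × SD), since the aim is "To determine the normal reference values of elastance and microvascularization ratio in the healthy lung"; and Faulkenberry-Weeks as the rule behind n. The article names that method in the analysis sentence, not in the sample-size sentence.

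**Criterion.** Choose k so that Pr(content ≥ 0.90) = 0.95. Then take the smallest n for which Pr(content ≥ P′) ≤ δ.

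**Formula.** Given the standardised error u of the sample mean, the content reaches p when (n − 1)s²/σ² exceeds (n − 1)·q(p; u²)/k². Here q(p; u²) is the p-quantile of a chi-square with 1 df and non-centrality u², and u ~ N(0, 1/n). The probability is the upper tail of a chi-square on n − 1 df, averaged over u by numerical integration.

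**Step 1: reproduce 60.** Several assignments of the two percentages were tried, all with P = 0.90 and confidence 0.95:

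| P′ | δ | n, two-sided exact | n, one-sided |
|---|---|---|---|
| 0.975 | 0.05 | **60** | 56 |
| 0.975 | 0.025 | 70 | 65 |
| 0.95 | 0.05 | 179 | 171 |
| 0.95 | 0.025 (plain reading) | **213** | 203 |
| 0.945 (5% relative, 0.90 × 1.05) | 0.025 | 275 | 263 |
| 0.925 | 0.05 | 865 | 836 |

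Only the first row gives 60, and it does so exactly: Pr(content ≥ 0.975) is 0.0508 at n = 59 and 0.0475 at n = 60. In that row 5% is the probability δ, and 2.5% is 1 − P′, the fraction of the population outside the larger content.

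**Step 2: what 60 subjects give on the plain reading.** At n = 60, k = 1.960 and k² = 3.841.

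- Content 0.95: Pr = 0.441, against the 0.025 implied by the wording, a ratio of 0.441/0.025 ≈ 18.
- Content 0.975: Pr = 0.0475.

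**Step 3: checks.** Replacing u² by its mean 1/60 gives a version that can be checked by hand.

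- Content 0.95: 59 × 3.905/3.841 = 59.98, and the upper tail of a chi-square on 59 df is 0.44.
- Content 0.975: 59 × 5.107/3.841 = 78.45, with upper tail 0.046.

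A simulation with 400,000 replicates at n = 60 gave 0.950, 0.440 and 0.048 for contents 0.90, 0.95 and 0.975. At n = 213 it gave 0.0249 for content 0.95. The chi-square and Howe approximations give 59 in place of 60 and 212 in place of 213.

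**The case against.** The strongest reply is that the number of subjects is not shown to be wrong. The article leaves both errors undefined, the definitions may stand in a cited source that is not at hand, and one assignment of the same two percentages returns exactly 60. This stands, and it rules out the stronger reading that a reader might draw: that Phase 1 is undersized and must recruit about 213 children. The 213 is only what the printed words would imply.

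The reply does not save the sentence. To recover 60, the error in tolerance has to be a probability and the error in confidence a fraction of the population, which inverts the way the same sentence has just used the two words. A reader could not work that out from the text.

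Two further objections stand:

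- **The 44% is not a defect of the interval.** An interval that must hold at least 90% with 95% confidence will usually hold more; at n = 60 its median content is about 94.7%. The 44% conflicts only with the printed precision, and rewording will not change it.
- **No patient is classified by these limits.** A reader might infer that over-wide limits would label abnormal lungs as normal. But section 2.1 assigns groups by clinical, ultrasound and blood findings. Section 2.7 compares groups by ANOVA or permutation test with a separate sample size, and the cut-off in section 2.2 is between pneumonia and atelectasis.

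Nor do the documents support a numerical criticism of the bootstrap branch: its method is not specified closely enough to compute. The choice of tolerance factor or of a transformation can properly be left to an analysis plan.

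**Conclusion.** The concern holds as a wrongly stated sample-size property. As worded, the precision is not what 60 subjects give: the chance of covering at least 95% of the population is about 44%, not 2.5%. What 60 subjects do give is a chance of just under 5% of covering 97.5% or more.

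This rests on a two-sided normal interval and on Faulkenberry-Weeks as the sizing rule. Sidedness does not alter the conclusion, since the plain reading needs 203 subjects one-sided. That the figures were mislabelled, with P′ = 0.975 and δ = 0.05 as the true inputs, is an inference from the exact match and is not stated in the article. The finding concerns the claim attached to the first outcome; it does not touch the Phase 2 comparisons.

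**What to change.** Keep 60 and replace the precision clause in section 2.7 with a statement of the property, for example: *With 60 subjects, a two-sided 90%/95% normal tolerance interval has at most a 5% chance of covering 97.5% or more of the population (P = 0.90, P′ = 0.975, δ = 0.05).* Add that this applies to the normal-theory branch only.

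The sponsor should first confirm from the original calculation that these were the inputs. If P′ = 0.95 with δ = 0.025 was really intended, 60 does not meet it and the number would need its own justification.

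The cost is one sentence, before the Phase 1 reference values are reported. Enrolment, data and analysis are unchanged. The drawback is that the stated precision becomes visibly less favourable than the present wording suggests.

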Considering that in BP, inflammation and alveolar filling with fluid and immune cells occur, leading to the hepatization of pulmonary tissue, while in atelectasis, there is alveolar collapse with a reduction in lung volume and tissue compression, our research group hypothesizes that BP will exhibit decreased pulmonary elasticity but a higher microvascularization ratio compared to atelectasis. Therefore, both SWE and SMI may play a crucial role in assessing these pathophysiological characteristics, thus contributing to the accurate characterization and diagnosis of these conditions. This hypothesis is supported by several studies conducted in adults. Lim et al. evaluated the elasticity of atelectasis and BP, among other lesions, and reported an elasticity of 2.51 ± 1.14 kPa in atelectasis and 19.98 ± 15.59 kPa in pneumonic consolidations. To date, no studies have been published regarding the microvascularization ratio in these lesions [23].

Up until now, the normal values of these imaging biomarkers and the role of these diagnostic tests have yet to be evaluated in the paediatric population. The ELASMIC study aims to analyze the ability of quantitative lung imaging biomarkers (elastance measured with SWE and microvascularization ratio measured with SMI) to discriminate between BP from other causes of lung consolidation such as atelectasis, reducing the need for invasive and radiation-based diagnostics in the paediatric population. As discussed previously, distinct values of elastance and microvascularization ratio are expected given the pathophysiological differences of each entity. The identification of statistically significant differences in imaging biomarkers between BP and atelectasis could significantly enhance the diagnostic approach to these disorders, offering a less invasive method and enabling a more precise quantitative characterization of the underlying pathological processes.

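### ANOVA with Tukey assumes a common variance that the article's own elastance figures contradict, and the permutation fallback does not by itself cure this

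*Protocol article*

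**What the plan says.** Section 2.7 of the protocol article plans a one-way ANOVA of each biomarker across BP, atelectasis and normal baseline, with Tukey's method if the ANOVA is significant. The alternative is: "If the conditions for the applicability of ANOVA are not met, a permutation test will be applied". The significance level is fixed: "A *p*-value of less than 0.05 will be considered statistically significant for all statistical tests". The sample size comes from the same model, "which gives a sample size of 53 subjects per group required to detect a medium effect size with 80% power and three groups", with the effect size set by convention: "Cohen suggested a value of 0.25 as a medium effect size".

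The Introduction gives the only elastance values by diagnosis. An adult study "reported an elasticity of 2.51 ± 1.14 kPa in atelectasis and 19.98 ± 15.59 kPa in pneumonic consolidations". For children it says that "the normal values of these imaging biomarkers and the role of these diagnostic tests have yet to be evaluated in the paediatric population", and for the second biomarker: "To date, no studies have been published regarding the microvascularization ratio in these lesions".

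Section 2.1 assigns patients to BP or atelectasis by final diagnosis, so the split between the two is not under the investigators' control. Section 2.2 lists both healthy versus consolidated lung and BP versus atelectasis as outcomes.

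**The concern.** ANOVA, Tukey's method and the calculation behind 53 per group all use one common within-group SD. The cited SDs differ by a factor of 13.7. When variances differ this much, a pooled standard error is too small for contrasts that involve the variable group (BP) and far too large for the contrast between the two tight groups. How far the error rate moves, and in which direction, then depends on the group sizes, which follow the case mix.

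The fallback looks like protection but need not be. A permutation test is exact when the groups have identical distributions under the null. If the means are equal but the variances differ, permuting an unstudentised statistic tests something other than equality of means. At stake are the 5% level that the article sets for all its tests, and the listed comparison of healthy with consolidated lung, where a real difference from atelectasis could be reported as none.

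**Working it through.** **1. The plan's own figure.** One-way ANOVA, k = 3, effect size 0.25 read as Cohen's f, alpha 0.05, noncentrality 3 × n × 0.25². Power is 79.7% at n = 52 and 80.5% at n = 53, so 53 per group is reproduced. The calculation assumes one common SD.

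**2. Inputs for the check.**
- Atelectasis 2.51 (SD 1.14) kPa and BP 19.98 (SD 15.59) kPa: Introduction, adult data.
- Sizes: 53 per group for ANOVA, and 60 healthy children for the tolerance intervals (section 2.7).
- Assumed, because the article gives no value: healthy SD 1.14 kPa (range 0.5 to 5), the healthy mean, and unequal BP/atelectasis splits.

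Sizes below are in the order healthy/atelectasis/BP.

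**3. Size of the violation.** (15.59 / 1.14)² = 13.7² = 187.

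**4. Standard errors at 60/53/53, healthy SD 1.14.**
- Pooled variance = (59 × 1.14² + 52 × 1.14² + 52 × 15.59²) / 163 = 78.4, so the pooled SD is 8.86 kPa.
- BP minus atelectasis: pooled SE = 8.86 × √(2/53) = 1.72; true SE = √((1.14² + 15.59²)/53) = 2.15. The pooled SE is 0.80 of the true one.
- Healthy minus atelectasis: pooled SE = 8.86 × √(1/60 + 1/53) = 1.67; true SE = 1.14 × √(1/60 + 1/53) = 0.215. The pooled SE is 7.8 times the true one.
- Tukey's critical difference for healthy versus atelectasis is 3.9 kPa. It stays at 3.9 to 4.2 kPa for a healthy SD from 0.5 to 5.

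**5. Type I error** (simulation, normal data, equal means, cited SDs, healthy SD 1.14):

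| Sizes | F-test | Tukey familywise | Permutation of ordinary F |
|---|---|---|---|
| 53/53/53 | 8.5% | 6.5% | 9 to 10% |
| 60/53/53 | 9.5% | 7.5% | about 10% |
| 60/73/33 | 22% | 21% | 22% |
| 60/33/73 | 3.1% | 2.1% | about 4% |

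Welch's ANOVA gives 4.6 to 5.0% in all four settings. At 60/53/53 each Tukey contrast with BP rejects in 6.4 to 7.2% of runs, against about 1.9% per contrast when variances are equal.

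**6. Other forms of the fallback.** A pairwise permutation of the BP-atelectasis mean difference is near nominal at 53:53 (5.3 to 5.5%), but rejects in 26% of runs with 80 atelectasis and 26 BP, and in 0.1% with 26 and 80. Permuting the studentised statistic gives 4.9 to 5.7% at every split tried.

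**7. Power at the cited SDs** (simulation, gamma data, healthy SD 1.14 or 3). Tukey power for healthy versus atelectasis by true difference:

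| Difference (kPa) | Tukey power |
|---|---|
| up to 2 | 0 to 0.2% |
| 3 | 7 to 9% |
| 4 | 53 to 59% |
| 5 | 92 to 94% |
| 6 | over 99% |

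At 1 kPa, Games-Howell has 98.5% power (healthy SD 1.14) or 50% (healthy SD 3). A pairwise permutation test at 0.05/3 has 98.4% (healthy SD 1.14). BP versus atelectasis at the cited means has about 100% power with Tukey and with Games-Howell.

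**The case against.** Several points on the other side stand.

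- **Tukey is conditional.** If equal variance is one of the checked conditions, SDs like these send elastance to the fallback: a Brown-Forsythe test rejected in every simulated run. A reader might infer from step 7 that the plan cannot separate healthy lung from atelectasis. The article does not support that. It gives no healthy mean, Tukey detects differences of 5 kPa or more well, and a pairwise permutation test would not share the loss.
- **The error can go either way.** A reader might infer that error for BP contrasts is always inflated. At equal sizes the inflation is modest, and it reverses if BP is the larger group.
- **The null is stylised.** It keeps both SDs while equating the means; normal data with mean 2.51 and SD 15.59 would be negative more than 40% of the time. Much of the spread follows the mean. The coefficients of variation are 1.14/2.51 = 0.45 and 15.59/19.98 = 0.78, which under a lognormal model imply a log-scale variance ratio of only about 2.5. This limits how literally the percentages can be taken, and it supports a log-scale analysis.
- **The evidence is narrow.** It is adult data on elastance, cited as background and not used for the sample size.
- **A condensed article may leave the permutation statistic and the pairwise procedure to an analysis plan.** That omission alone is no fault, and a studentised version would fit the wording.

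What remains is that the stated first-line method rests on an assumption that the article's own figures contradict, and that the stated remedy works only in particular forms and allocations unless the statistic is studentised.

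**Conclusion.** The point holds in limited form. Under the cited adult SDs, neither the ANOVA F-test nor a permutation of the ordinary F holds the 5% level for elastance: about 8.5% to 10% at the planned sizes, and from about 3% to 22% as the BP/atelectasis split varies. Tukey's familywise error is about 6.5 to 7.5% at the planned sizes. If pooled Tukey is used, differences between healthy lung and atelectasis below about 4 kPa would mostly be missed.

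These figures rest on an assumed healthy SD of 1.14 kPa, equal means with unequal SDs for the error rates, and adult SDs carrying over to children. The power to distinguish BP from atelectasis at the cited means is not in doubt, and no conclusion is drawn for the microvascularization ratio. This should be changed because a better method is nearly free; it does not undermine the study.

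**What to change.** Prespecify Welch's ANOVA with Games-Howell pairwise comparisons for the contrasts among BP, atelectasis and healthy lung, used from the start without a variance pre-test, and on log elastance if the data are skewed. In simulation at 53/53/53 and 60/53/53, Games-Howell's familywise error was 3.9 to 4.5%. If a resampling test is preferred, permute the studentised (Welch) statistic and state how multiplicity is controlled across the three pairs.

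The cost is a few sentences in section 2.7 or the analysis plan, no additional patients, and a very small loss of power if the variances turn out equal. The change should be made before the data are analysed.

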## 3. Limitations

One of the main limitations of this project is that it is a single-centre study. However, it is a tertiary paediatric hospital that handles a high volume of patients, making the sample potentially large and representative at the population level. A potential selection bias in Phase 1 may arise from evaluating imaging biomarkers in patients who present to the hospital for reasons unrelated to pulmonary consolidation. This could limit the generalization of normal value results to the general population. Another limitation of the study is the potential for artifacts in biomarker measurements due to the presence of air in non-consolidated pulmonary tissue. If this issue occurs, it cannot be addressed by adjustments to the biomarker acquisition technique and would affect Phase 1 of the study. In this phase, it may be concluded that SWE and SMI are not reliable pulmonary diagnostic tools in the absence of consolidation. This could serve as a key preliminary finding of the study. In contrast, in Phase 2, where consolidated (non-aerated) pulmonary tissue is being assessed, the presence of air is unlikely to cause measurement artifacts. Another relevant aspect is the potential inter-observer variability, although this is not included among the objectives of the ELASMIC study, and thus, imaging biomarkers will be acquired by a single examiner. However, given that the examiner is a highly qualified professional trained in LUS image acquisition, the study assumes minimal inter-observer variability (the differences in measurements taken by another observer are negligible and clinically insignificant) and minimal intra-observer variability (the differences in measurements taken by the same examiner are negligible and clinically insignificant). Another limitation, which also represents a strength due to its innovative potential, is the use of diagnostic techniques that are not conventionally employed for evaluating lung tissue. In this regard, significant differences in the manual pressure exerted by the operator with the transducer could modify the measured results. Therefore, it will be essential to apply minimal pressure and verify the stability of the color map prior to the acquisition of the biomarkers.

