### 2.2. Outcomes

Determine normal values for the imaging biomarkers (elastance and microvascularization) in healthy lung parenchyma and within different healthy areas.Determine the values for the imaging biomarkers (elastance and microvascularization) in lung consolidation.Evaluate differences between the imaging biomarker values on healthy lung vs. consolidated lung.Evaluate differences between the imaging biomarker values of group 1 (BP) vs. group 2 (atelectasis). This would allow the establishment of a cut-off point for the etiological differentiation of lung consolidations.

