ELASMIC aims to update and enhance current protocols for diagnosing BP and other pulmonary consolidations. Specifically, it seeks to reduce the reliance on CXR while maintaining the current role of LUS in detecting various pulmonary consolidations. Furthermore, SWE and SMI could play a crucial complementary role to LUS in characterizing these pulmonary consolidations and providing etiological guidance. To achieve this, it is essential to determine the normal values for lung elastance and microvascular patterns in healthy lung tissue. These baseline values will enable the assessment of non-invasive biomarkers in patients with lung consolidation, ultimately facilitating differentiation between various potential causes. Standardized image acquisition and biomarker measurement will help reduce operator-dependent variability. Despite the limitations mentioned, achieving the study’s objectives could significantly improve clinical management through a quantifiable and non-invasive approach. Moreover, it may optimize therapeutic strategies by reducing the use of empirical antibiotics in patients without bacterial infections, which could have a substantial positive impact on global health.

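### Healthy-lung readings that the plan concedes may be unreliable still enter the single three-group test that leads to BP vs atelectasis, so a Phase 1 failure can carry into Phase 2

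*Protocol article*

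**What the plan says.** Section 3 (Limitations) names "the potential for artifacts in biomarker measurements due to the presence of air in non-consolidated pulmonary tissue" as a risk and says of it that "it cannot be addressed by adjustments to the biomarker acquisition technique and would affect Phase 1 of the study". The consequence it draws is that "it may be concluded that SWE and SMI are not reliable pulmonary diagnostic tools in the absence of consolidation". For consolidated tissue in Phase 2 it expects no such trouble: "the presence of air is unlikely to cause measurement artifacts".

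Section 2.7 sets one comparison across the disease groups: "among the different groups (BP, atelectasis, and normal baseline), analysis of variance (ANOVA) will be performed". The pairwise step is conditional: "In the event of finding significant differences, post-hoc analysis will be conducted using Tukey’s method". If the ANOVA conditions fail, a permutation test replaces it, and no pairwise step is named after that. The size is 53 per group, for three groups, a medium effect of 0.25 and 80% power, with significance at 0.05.

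Section 2.2 lists "Evaluate differences between the imaging biomarker values on healthy lung vs. consolidated lung" as one outcome and BP vs atelectasis as another. The Discussion adds that "it is essential to determine the normal values for lung elastance and microvascular patterns in healthy lung tissue".

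The article does not say what happens to the three-group comparison if Phase 1 finds the readings unreliable.

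**The concern.** The two statements do not fit together. Section 3 confines the artefact to Phase 1, but section 2.7 carries the Phase 1 readings into the Phase 2 test. Two separate harms can follow, from two different properties of the artefact.

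- **Shift in the healthy mean.** Healthy vs consolidated then contrasts artefact with tissue, and a small p-value says nothing about disease.
- **Extra spread in the healthy group.** This enters the pooled error of the ANOVA and Tukey step, and the reference distribution of the three-group permutation test. It weakens BP vs atelectasis, the comparison that needs no healthy readings and on which the diagnostic cut-off rests.

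**Working it through.** **Inputs from the protocol article.** Three groups, 53 per group, alpha 0.05, effect size 0.25, 80% power (section 2.7). Adult elastance 2.51 ± 1.14 kPa in atelectasis and 19.98 ± 15.59 kPa in pneumonia (Introduction). Elastance scale 40 kPa (section 2.4.2).

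**Assumptions.** The documents give no size for the artefact. The healthy shift is taken as 0.5 or 1 SD, and the healthy SD as 1 to 3 times that of the consolidation groups. The true BP–atelectasis difference is 0.6 SD, with healthy midway. It lies between 0.53 and 0.61 SD, two patterns that both give f = 0.25 (healthy equal to atelectasis: 0.25 × 3/√2 = 0.53; healthy midway: 0.25 × √6 = 0.61).

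**1. The plan's own figure.** For a one-way ANOVA with f = 0.25, the noncentrality is 3 × n × 0.25². At n = 53 this is 3 × 53 × 0.0625 = 9.94, and power is 80.5%. At n = 52 it is 79.7%. So 53 per group reproduces.

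**2. Shift only, no disease difference.** BP and atelectasis are equal and the healthy group is displaced by artefact. In simulation, a 0.5 SD shift makes a healthy-vs-consolidated Tukey contrast significant in about 73% of trials, and a 1 SD shift in about 100%. At a shift of 0.53 SD, f = 0.53 × √2/3 = 0.25, so the planned 80% omnibus power can come wholly from the artefact group. If artefact adds noise but no shift, such contrasts appear in only 5–6% of trials.

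**3. Spread: the mechanism.** In SD units of the consolidation groups, the pooled error variance is (1 + 1 + r²)/3, where r is the healthy SD ratio. The Tukey critical difference is 3.346 × √(pooled variance/53).

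| r | pooled variance | observed difference needed |
|---|---|---|
| 1 | 1.00 | 0.46 SD |
| 1.5 | 1.42 | 0.55 SD |
| 2 | 2.00 | 0.65 SD |
| 3 | 3.67 | 0.88 SD |

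A direct two-group test needs about 1.983 × √(2/53) = 0.39 SD, whatever the healthy readings do.

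**4. Spread: power at a 0.6 SD difference.**

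| r | ANOVA then Tukey, BP vs atelectasis | permutation fallback, omnibus | direct two-group test |
|---|---|---|---|
| 1 | 75% | 80% | 85–88% |
| 1.5 | 59% | 66% | 85–88% |
| 2 | 39% | 48% | 85–88% |
| 3 | 8% | 26% | 85–88% |

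The permutation figures carry a few points of simulation error; a run of 3,000 trials gave 79%, 66%, 52% and 25%. The omnibus figure is a ceiling for any pairwise step made conditional on it.

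**5. Which column applies.** At ratios 2 and 3, Levene's test rejects equal variance in 99.9% and 100% of trials, so the fallback governs and 39% and 8% would almost never arise. At 1.5 it rejects in about 79% of 2,000 simulated trials, so 59% applies only where the check passes.

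**6. Elastance with the cited adult values.** The pooled SD is √((1.14² + 15.59²)/2) = 11.05, so the difference is (19.98 − 2.51)/11.05 = 1.58 SD. With artefact readings held within 0–40 kPa, ANOVA-then-Tukey power for BP vs atelectasis stays near 100%. At half that difference it is 95%, against 98% for the direct test.

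**The case against.** The strongest defence has four parts.

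**The plan has a fallback.** Unequal variances lead to the permutation test. That stands, and a reader who takes the Tukey powers of 39% and 8% as the plan's performance goes too far. The fallback still loses power, because the healthy readings remain in the statistic, and the article names no route from it to BP vs atelectasis. That pairwise step may be in an analysis plan not shown; the conditional three-group structure is fixed here.

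**The only effect figures given make masking negligible for elastance.** This also stands if the adult values apply to children. The article says neither biomarker has been evaluated in children and that no values are published for the microvascularization ratio in these lesions. For that ratio the risk can be neither bounded nor dismissed.

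**The risk is disclosed.** True, and a careful reader told that the tools fail in aerated lung would discount healthy vs consolidated. Disclosure does not take the readings out of the test.

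**The SWE reading filter in section 2.4.2 may help.** It may, but nothing says that it removes air artefact, and none is stated for SMI.

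A reader might infer that a Phase 1 failure necessarily yields a false result or hides BP vs atelectasis. The documents do not support that: the first needs a mean shift and the second needs extra variance. A pure shift leaves Tukey power at about 78% at a 0.61 SD difference. Nor do they suggest that the consolidated readings themselves are corrupted.

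**Conclusion.** The point holds in conditional form. The article names a circumstance in which one group's readings are invalid, treats the other phase as unaffected, and fixes a test that joins the two. Under the stated assumptions, a 0.5 SD shift gives a significant healthy contrast without disease in about 73% of trials. A doubled or tripled healthy SD takes the fallback's omnibus power from about 80% to about half or a quarter, while a direct test keeps 85–88%. The artefact sizes are assumed throughout. The masking part matters chiefly for the microvascularization ratio, and for elastance only if the paediatric difference is far smaller than the adult one. The interpretation of healthy vs consolidated is exposed for both biomarkers.

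**What to change.** In section 2.7:

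1. Make a direct two-group comparison of BP and atelectasis (unequal-variance or permutation) the test of that outcome, neither conditional on the three-group test nor pooled with the healthy group.
2. State that if Phase 1 concludes SWE or SMI is unreliable in aerated lung, then for that biomarker the healthy group is left out of the Phase 2 comparison, healthy vs consolidated is not read as a disease effect, and no normal limits are derived.
3. Have the investigators set the criterion for that conclusion before Phase 1 data are seen. The documents offer no basis for a particular threshold, so none is proposed here.

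The cost is a few sentences and no new measurements for the direct test. The normal-value and healthy-vs-consolidated outcomes may have to be declared unanswerable. Power for BP vs atelectasis must be stated separately: 53 per group gives about 72% at a 0.5 SD difference and 86% at 0.6 SD; 80% at 0.5 SD would need 64 per group.
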